### Control arm

In the control arm, patients will not be informed about the MEDOCC-CrEATE trial and receive routine follow-up care consisting of CEA tests every 3 months for the first 3 years and abdominal ultrasound or CT every 6 months in the first year and once a year afterwards. One year after surgery a colonoscopy is performed. Post-surgery blood samples will not be tested for ctDNA immediately, but will be analyzed batch-wise after several months without result disclosure to patients and their treating physicians.

### Follow-up

Blood samples will be collected at 6-monthly intervals for the first 3 years after surgery for both patients in the experimental arm and the control arm conform the MEDOCC study protocol. These samples will not be analyzed for ctDNA immediately and results will not be disclosed to patients and treating physicians.

### Tumor tissue-informed ctDNA analysis

After surgery the local pathologist will send a formalin-fixed paraffin-embedded (FFPE) tissue block to the central laboratory, where DNA will be isolated for further analysis.

The post-surgery blood sample is drawn between 4 and 21 days after surgery. The sample is not withdrawn before day 4 to reduce the risk of false-negative ctDNA tests due to the relatively large amount of cell free DNA (cfDNA) released due to cell damage after surgery. The blood is taken no later than 21 days after surgery to be able to start chemotherapy within 12 weeks after surgery. Samples are kept at room temperature and sent by regular mail to the central laboratory within 1–2 days, where ctDNA will be isolated for further analysis.

Tumor tissue DNA will be analyzed by targeted next generation sequencing of a panel of more than 500 genes using the PGDx elio™ tissue complete assay from Personal Genome Diagnostics (PGDx, Baltimore, MD, USA). Plasma ctDNA will be analyzed by targeted next generation sequencing of a panel of more than 30 genes using the PGDx elio™ plasma resolve assay from PGDx (Baltimore, MD, USA). Both panels include the most commonly mutated genes in CC, including *APC*, *TP53*, *KRAS* and *BRAF*. Tumor tissue DNA mutations are used as input information for plasma ctDNA mutation calling, thereby increasing both sensitivity and specificity of the ctDNA test.

### Primary endpoint

The primary endpoint is the proportion of patients starting with ACT after detection of ctDNA in the post-surgery sample.

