## Abstract

**Background:**

Accurate detection of patients with minimal residual disease (MRD) after surgery for stage II colon cancer (CC) remains an urgent unmet clinical need to improve selection of patients who might benefit form adjuvant chemotherapy (ACT). Presence of circulating tumor DNA (ctDNA) is indicative for MRD and has high predictive value for recurrent disease. The MEDOCC-CrEATE trial investigates how many stage II CC patients with detectable ctDNA after surgery will accept ACT and whether ACT reduces the risk of recurrence in these patients.

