**Discussion:**

The MEDOCC-CrEATE trial will provide insight into the willingness of stage II CC patients to be treated with ACT guided by ctDNA biomarker testing and whether ACT will prevent recurrences in a high-risk population. Use of the TwiCs design provides the opportunity to randomize patients before ctDNA measurement, avoiding ethical dilemmas of ctDNA status disclosure in the control group.

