## Methods/design

### Aim

This study investigates the willingness of patients to receive ACT after detection of ctDNA post-surgery and the effect of ctDNA-guided ACT on the RR in stage II CC patients.

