### Experimental arm

After randomization, only patients randomized to the experimental arm will be asked separate informed consent for the immediate analysis of ctDNA status of the post-surgery sample. A small proportion of patients, estimated approximately 5–8% will have detectable ctDNA in their blood. These patients will be offered ACT. Patients decide whether they accept or refuse this treatment. Patients without detectable ctDNA will receive routine standard of care.

ACT will consist of 6 months of capecitabine and oxaliplatin (CAPOX) or 6 months of fluorouracil, leucovorin and oxaliplatin (FOLFOX). Treatment starts preferably within 8 weeks and not beyond 12 weeks after surgery.

During and after completing ACT routine follow-up will consist of regular visits at the surgical outpatient department, blood withdrawals for analysis of carcinoembryonic antigen (CEA) and imaging (standard ultrasound of the liver) according to current guidelines in the Netherlands. No additional imaging will be performed to prevent detection bias.

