### Data analysis

Data will be analyzed according to the intention-to-treat principle for the primary endpoint and the secondary endpoint of 2-year RR in patients with detectable ctDNA after surgery. In this analysis we expect to compare 30 patients with detectable ctDNA who received ACT in the intervention arm with 30 patients with detectable ctDNA in the control arm, i.e. based on ctDNA analysis performed retrospectively, at least 3 months after surgery, and not disclosed to patients and treating physicians. The proportion of patients that experience a recurrence in both arms will be compared by means of a chi-square test. In addition, for other secondary endpoints and exploratory analyses we will analyze time-to-event outcomes in patients in both arms with detectable ctDNA after surgery. Differences in time-to-event outcomes will be analyzed by standard survival methods, e.g. Kaplan-Meier curves compared by log-rank tests. Cox’s proportional hazards models will be used for multivariable analysis.

Comparison of QoL of the ctDNA positive patients in both study arms will be done using repeated measurements methods and including ACT as factor. QoL will also be analyzed for the whole population in both arms of the study. Treatment differences at each QoL assessment time point will be compared by means of the Wilcoxon Rank Sum Test.

A lifetime horizon will be applied for the cost-effectiveness analysis, parametric survival functions will be used to extrapolate DFS and OS curves beyond 5 years.

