This study has also potential limitations and challenges. The TwiCs design is potentially susceptible to low statistical power and internal validity biases. Levels of participant’s eligibility and consent should be substantial to achieve valid and reliable results, and measurements taken in the control group should be sufficient for adequate comparisons to be made [33]. Therefore the TwiCs design is not appropriate for every experimental intervention. In case of the MEDOCC-CrEATE study, we argue that eligibility and also consent will be substantial because of the high incidence of CC, the large cohort with high inclusion rates and the assumption that eligible patients in the intervention group are willing to accept ACT because of the very strong association of the presence of ctDNA with recurrent disease.

Another limitation is the small sample size for primary outcome analysis. Eventually only 30 patients in both arms of the trial are expected to have detectable ctDNA after surgery. Based on previous data, 80% relapses are expected within 2 years, and with a high event rate small numbers are sufficient [21].

We recommend a 6-month duration of ACT consisting of capecitabine and oxaliplatin (CAPOX) or fluorouracil, leucovorin and oxaliplatin (FOLFOX) for patients with detectable ctDNA after surgery. The first adjuvant CC trials investigating the combination of a fluoropyrimidine and oxaliplatin reported results for 6 month duration of ACT [34]. In 2018 the IDEA trial found a large reduction in toxicity for 3 months treatment compared to 6 months treatment. Although this trial could not confirm non-inferiority for 3 months treatment for all patients treated with CAPOX or FOLFOX in stage III CRC, the small difference limits clinical relevance. Besides, it did show non-inferiority of the shorter regimen in patients treated with CAPOX. Consequently, Dutch guidelines recommend 3 months of ACT for CC since 2019. However, among patients with highest risk of recurrence (T4, N2, or both) superiority of 6-month duration of therapy was found. Additional IDEA-FRANCE results, presented at the ESMO Congress 2019, showed the worst prognosis for ctDNA positive patients who only received 3 months of ACT [35]. Therefore in this study, we recommend 6-months ACT for patients with a very high risk of disease recurrence due to the presence of ctDNA after surgery.

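### The primary endpoint measures uptake of chemotherapy among patients who agreed to ctDNA testing; this fits the stated aim, but not the intention-to-treat label or the abstract's conclusion about the whole test-guided strategy

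*Protocol article*

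**What the plan says.** The Primary endpoint section reads: "The primary endpoint is the proportion of patients starting with ACT after detection of ctDNA in the post-surgery sample". The Experimental arm section puts a consent step before any result exists: "only patients randomized to the experimental arm will be asked separate informed consent for the immediate analysis of ctDNA status". Patients found positive are then offered ACT and may accept or refuse it.

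The article describes what this endpoint is for in two ways:

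- **After detection.** The Aim section speaks of the "willingness of patients to receive ACT after detection of ctDNA post-surgery". The abstract's Background says the trial "investigates how many stage II CC patients with detectable ctDNA after surgery will accept ACT".
- **Whole strategy.** The abstract's Discussion promises insight into the "willingness of stage II CC patients to be treated with ACT guided by ctDNA biomarker testing".

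On the analysis population, Data analysis says: "Data will be analyzed according to the intention-to-treat principle for the primary endpoint". Sample size considerations assumes that 90% of intervention-arm patients with detectable ctDNA will be treated, and does not restrict this to those who consent to testing.

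Later testing of stored samples is described in the Control arm section only, where post-surgery samples "will be analyzed batch-wise after several months without result disclosure to patients and their treating physicians". No equivalent is described for experimental-arm patients who decline immediate testing.

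**The concern.** A patient who declines the test has no detected result, so the endpoint as worded cannot count that patient, either as accepting or as refusing. If some patients decline because they do not want chemotherapy, their refusal of the strategy drops out of a figure meant to describe patients' willingness.

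The article itself makes such a link plausible. The main Discussion expects substantial consent partly because of "the assumption that eligible patients in the intervention group are willing to accept ACT". If willingness to have ACT supports consent to the test, unwillingness may lead to refusal of the test.

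What is at stake is how the headline is read. A result near 90% would be correct for tested positives. Read as acceptance of ctDNA-guided treatment among all patients offered it, it could be too favourable, and the intention-to-treat label would encourage that reading.

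**Working it through.** **Inputs from Sample size considerations.** Uptake u = 0.90; 30 ctDNA-positive patients per arm; ctDNA prevalence 5%; 660 patients per arm; margin of error 11%.

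**Assumed inputs.** d is the share of ctDNA-positive experimental-arm patients who decline testing. The article gives no figure, so 10%, 20% and 30% are used. q is the share of those decliners who would have started ACT. It is also not given, and is varied from 0 to 0.90.

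**1. The plan's own precision.** Wald half-width at n = 30: 1.96 × √(0.90 × 0.10 / 30) = 0.107, which rounds to the stated 11%. (The article calls this the width of the interval; it is the half-width.)

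**2. The plan's expected positives.** 30 / 0.05 = 600, and 600 × 1.10 = 660 per arm. Then 660 × 0.05 = 33 expected positives, which treats every experimental-arm patient as tested. The 10% allowance names loss to follow-up and rejection of adjuvant therapy, not refusal of the test.

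**3. Acceptance over all positives.** A = u(1 − d) + q·d, with u = 0.90:

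| Test refusal d | Endpoint as worded | A, q = 0 | A, q = 0.45 | A, q = 0.90 | Largest gap |
|---|---|---|---|---|---|
| 10% | 90% | 81% | 85.5% | 90% | 9 points |
| 20% | 90% | 72% | 81% | 90% | 18 points |
| 30% | 90% | 63% | 76.5% | 90% | 27 points |

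Example: d = 0.20 and q = 0 gives 0.90 × 0.80 = 0.72. The endpoint reads 90% in every row. With q = 0 the gap is 0.90·d, which exceeds the planned half-width once d is above 0.107 / 0.90 = 0.119, about 12% refusal. With q = 0.90 there is no gap at any d.

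**4. Effect on precision.** Of the 33 expected positives, 29.7, 26.4 or 23.1 are tested at 10%, 20% or 30% refusal. The half-width becomes 10.8, 11.4 or 12.2 points. This loss is small; what matters is which patients the figure describes.

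**5. Whether the lower bound can be estimated.** Let c be the test-consent rate among all 660 experimental-arm patients and m the number of tested positives. The estimate is c·u, with delta-method variance c²·u(1 − u)/m + u²·c(1 − c)/660. At c = 0.80 and m = 26.4:

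- 0.64 × 0.09 / 26.4 + 0.81 × 0.16 / 660 = 0.00218 + 0.00020 = 0.00238
- standard error 0.0488, half-width 1.96 × 0.0488 = 9.6 points around 72%

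The calculation uses the overall consent rate for the positives. That is reasonable because patients decide before they know their result.

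**The case against.** The strongest reply is that the endpoint answers the question the trial asks. The Aim section concerns willingness after detection, and the abstract's Background likewise speaks of patients with detectable ctDNA. This stands: against that aim, the endpoint is not biased. Only the abstract's Discussion is worded for the strategy as a whole.

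Second, agreeing to the test commits nobody to chemotherapy. The article expects about 5–8% of patients to be positive, so most tested patients would receive no offer, and those who do may still refuse. Patients may decline for unrelated reasons. This also stands, and it is why the lower end of each range is an extreme.

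Third, the article acknowledges that consent levels must be substantial, and the handling of decliners may be set out in a fuller document. This stands in part. The absence of such detail is no fault in an article. The difficulty lies in what is stated: an endpoint conditional on detection, an intention-to-treat label for that same endpoint, and a conclusion about the strategy.

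Two stronger readings might be inferred. One is that acceptance is overstated as a matter of fact. The article gives neither a refusal rate nor reasons for refusal, so the gap may be zero. The other is that consent rate times uptake should become the headline. It counts every test refusal as refusal of chemotherapy, so it bounds willingness from below and does not estimate it.

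**Conclusion.** The point holds as a mismatch between the endpoint and two statements made about it. The endpoint gives uptake among tested ctDNA-positive patients. It fits the Aim section. It does not fit the intention-to-treat label, because consent given after randomisation decides who can be counted, and it does not support the strategy-level conclusion in the abstract.

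Acceptance of the strategy may be overstated by 0 to 9, 0 to 18 or 0 to 27 points at 10%, 20% or 30% test refusal. These figures rest on the plan's 90% uptake, on assumed refusal rates, and on decliners being no more willing to have ACT than tested patients. The concern is limited to this single-arm endpoint; nothing here bears on the comparison of recurrence between the arms.

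**What to change.** 1. Keep the endpoint, and label it uptake of ACT among tested ctDNA-positive patients.
2. For this endpoint, either drop the intention-to-treat label or define the denominator it refers to.
3. Report beside it the test-consent rate among all patients randomised to the experimental arm.
4. Report consent rate × uptake with a delta-method or bootstrap interval, described as the lower bound in which decliners count as non-acceptors.
5. Limit the willingness conclusion in the abstract's Discussion to tested patients unless the lower bound also supports the wider statement.

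The cost is a change of wording and one further calculation from allocated arm, test consent and ACT start. No sample from decliners is needed, and the sample size and patient care do not change. The downside is a less favourable supporting figure, which is conservative because some decliners might have accepted ACT; the report should say so.

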### Secondary endpoints

The most important secondary endpoint is 2-year RR in patients with detectable ctDNA in their blood, expressed as the proportion of patients that experience a recurrence within 2 years after surgery. Detection of recurrences (in months after surgery) will occur by standard follow-up investigations including 3–6 monthly blood sampling of tumor marker CEA and 6 monthly imaging with ultrasound liver or CT abdomen and when indicated by symptoms. Radiological and/or histopathological evidence is used to confirm the recurrence; the date of the said investigation is considered the date of recurrence.

Data about follow-up, recurrences and survival are routinely collected within PLCRC using the Netherlands Cancer Registry (NCR), managed by the Netherlands Comprehensive Cancer Organisation (IKNL) to provide insight in the characteristics and magnitude of cancer in the Netherlands [28].

Other secondary endpoints include 2-year RR in a per-protocol analysis, 5-year RR (intention-to-treat and per-protocol analysis), time to recurrence (TTR), 2- and 5-year disease free survival (DFS) rate, 5- and 7-year disease-related OS rate, 2- and 5-year RR in patients with undetectable ctDNA after surgery, quality of life (QoL) and cost-effectiveness of the ctDNA-guided strategy.

#### Time-to-event outcomes

OS rate is expressed as proportion of patients that are alive 5 and 7 years after surgery. DFS rate is expressed as proportion of patients that did not experience disease recurrence, a second primary CC or death within 2 and 5 years after surgery. TTR is expressed as time (months) between surgery and detection of disease recurrence. Patients will be censored at the last date of follow-up if a date of death is not recorded and at the date of death if the cause of death is not due to CC.

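### One censoring rule, tied to no endpoint, censors deaths not due to colon cancer and so conflicts with the definition of OS and, unless meant for TTR alone, of DFS

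*Protocol article*

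**What the plan says.** All places are in the protocol article.

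- **OS**, under Time-to-event outcomes: "OS rate is expressed as proportion of patients that are alive 5 and 7 years after surgery". The cause of death is not restricted.
- **DFS**, same paragraph: the proportion who "did not experience disease recurrence, a second primary CC or death within 2 and 5 years after surgery". Again the cause of death is not restricted.
- **TTR**, same paragraph: "TTR is expressed as time (months) between surgery and detection of disease recurrence".
- **Censoring**, the sentence that follows TTR and ends the paragraph: a patient with no recorded death is censored at last follow-up, "and at the date of death if the cause of death is not due to CC". No endpoint is named.
- **Endpoint list**, under Secondary endpoints: "5- and 7-year disease-related OS rate".
- **Use**, under Data analysis: time-to-event outcomes in ctDNA-positive patients are analysed by standard survival methods, for example "Kaplan-Meier curves compared by log-rank tests", with Cox models for multivariable analysis. The DFS and OS curves are also extrapolated past 5 years for a lifetime cost-effectiveness analysis.

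**The concern.** All-cause survival and disease-specific survival are different estimands, and the article states both under the name OS. An analyst who follows the definition counts a death from another cause as an event. One who follows the censoring rule removes that patient from the risk set. For DFS the rule, if it applies, takes out a component that the definition includes.

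The direction of the error is known: leaving out deaths raises the DFS and OS curves. Two consequences depend on further conditions. First, adjuvant chemotherapy (ACT) is offered only in the experimental arm. If a death from its toxicity were coded as not due to colon cancer, it would be censored, and the comparison would tilt towards that arm. Second, if the curves extrapolated for cost-effectiveness are the censored ones and mortality from other causes is not added back, life-years are overstated.

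**Working it through.** The article gives no figure to reproduce on this point. The check compares the texts and then sizes the effect under stated assumptions.

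**1. How each text treats a death not due to colon cancer, in a patient without recurrence**

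| Text | Treatment of the death |
|---|---|
| OS definition (Time-to-event outcomes) | event |
| DFS definition (same paragraph) | event |
| Censoring rule (same paragraph) | censored |
| Disease-related OS (Secondary endpoints) | censored, on the usual meaning of the term |
| TTR definition | not an event; censoring is conventional |

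Rows 1 and 3 cannot both be applied to OS. Rows 2 and 3 conflict if the rule reaches DFS. Rows 1 and 4 conflict whatever the scope of the rule.

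**2. Scope of the rule**

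The sentence opens with "Patients will be censored at the last date of follow-up if a date of death is not recorded and at the date of death if", and the condition that completes it is a cause other than colon cancer. Its first half makes an unrecorded death the condition for censoring at last follow-up, which is how a rule for a survival endpoint is worded. Read literally for TTR, it would also censor a patient who has recurred and is still alive. The section heading covers all the outcomes. The position directly after TTR points the other way.

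**3. Illustration: one to three early deaths in the experimental arm**

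Inputs from Sample size considerations: 30 ctDNA-positive patients per arm; 79% recurrence at 2 years without ACT; an absolute reduction of 30 points, so 79% − 30% = 49% with ACT. Assumptions: k deaths not due to colon cancer occur before any recurrence, recurrence is the only other DFS event, and no other deaths occur for the OS column.

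- Deaths censored: 2-year DFS = 1 − 0.49 = 51.0% for every k.
- Deaths counted: 2-year DFS = (1 − k/30) × 0.51.
- OS overstatement = k/30.

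| k | DFS, counted | DFS, censored | DFS overstated by | OS overstated by |
|---|---|---|---|---|
| 0 | 51.0% | 51.0% | 0 | 0 |
| 1 | 49.3% | 51.0% | 1.7 points | 3.3 points |
| 2 | 47.6% | 51.0% | 3.4 points | 6.7 points |
| 3 | 45.9% | 51.0% | 5.1 points | 10.0 points |

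**4. Illustration: the same other-cause mortality in both arms**

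Let d be the assumed 5-year mortality not due to colon cancer, with constant, independent hazards. Then 2-year DFS = (1 − recurrence) × (1 − d)^(2/5).

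| d | ACT arm | Control arm | Difference |
|---|---|---|---|
| 0, or deaths censored | 51.0% | 21.0% | 30.0 points |
| 5% | 50.0% | 20.6% | 29.4 points |
| 10% | 48.9% | 20.1% | 28.8 points |
| 15% | 47.8% | 19.7% | 28.1 points |

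With equal mortality in the arms, both curves move down together and the contrast loses 0.6 to 1.9 points. An excess of such deaths in one arm, as in step 3, is what distorts the comparison.

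**The case against.** The strongest defence is that the sentence belongs to TTR alone. It follows the TTR definition and can be read as covering patients without recurrence: those still alive are censored at last follow-up, and those who died of another cause at death. The missing date of death then only identifies who is alive. On that reading the DFS definition is intact. This is possible, and for that reason the DFS conflict is conditional. It does not clear OS, because the endpoint list and the definition still name different quantities.

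A second defence is that disease-related OS was intended, which makes the rule coherent for that endpoint. Then the definition by being alive is wrong, and the scope for DFS is still open.

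A third is that a condensed article leaves censoring detail to the full protocol or SAP. That would answer a complaint of missing detail. Here a stated rule conflicts with a stated definition, and a SAP that follows the article has to break one of them.

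Several stronger readings are tempting, and the article does not support them:

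- **That the survival endpoints are blind to fatal ACT toxicity.** The article gives no rule for attributing treatment-related deaths and no rate for them. The loss occurs only if such deaths are coded as not due to colon cancer.
- **That reported OS is several points too high.** Taking 60% cancer-specific survival and 5% to 15% other-cause mortality gives 0.60 × 0.95 = 57% and 0.60 × 0.85 = 51%, a gap of 3 to 9 points. Every input there is assumed, and the gap is a shift in the level of a curve, not a bias between the arms.
- **That the TTR test is wrong.** A log-rank test that censors competing deaths already compares cause-specific hazards. Only a Kaplan-Meier estimate of recurrence incidence is overstated.
- **That the cost-effectiveness result is wrong.** The article does not say which OS curve is extrapolated, or whether other-cause mortality is added.

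**Conclusion.** The inconsistency is real. For OS, the definition cannot be applied together with the censoring rule, nor squared with the disease-related label in the endpoint list. For DFS, the definition and the rule conflict unless the rule is confined to TTR, a reading that its position allows but that its wording and the section heading do not favour.

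Applied as written, the rule makes DFS and OS too favourable by an amount that the article does not allow anyone to compute. The figure of about 3.3 points of OS and 1.7 points of 2-year DFS per early death is illustrative. It rests on 30 patients, the planning recurrence of 49%, and the assumption that the death precedes any recurrence. The effect is small if such deaths are rare.

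The primary endpoint, the chi-square comparison of 2-year recurrence and the power calculation built on it are untouched. Severity is moderate, since only other secondary endpoints and the cost-effectiveness extrapolation are exposed.

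**What to change.** Replace the single sentence with a rule for each endpoint:

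- **OS:** death from any cause is an event; censor only at last follow-up.
- **DFS:** recurrence, second primary colon cancer or death from any cause is an event; censor only at last follow-up.
- **TTR:** keep censoring deaths not due to colon cancer for the log-rank and Cox comparison, and report recurrence incidence with those deaths as a competing event.
- **Disease-specific survival:** if wanted, list it under its own name beside OS, with a rule for classifying treatment-related deaths.
- **Cost-effectiveness:** state that all-cause OS is the curve to be extrapolated.

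Then reconcile the OS label in Secondary endpoints with the definition.

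The cost is wording in the protocol and SAP, best settled before outcome data are analysed. Survival data already come through the national cancer registry. The article does not say whether the registry records cause of death finely enough to identify treatment-related deaths, so the attribution rule may need a brief check of that source.
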